## Abstract

**Background:**

Improved organization of trauma care in the acute phase has reduced mortality of trauma patients. However, there has been limited attention for the optimal organization of post-clinical rehabilitation of trauma patients. Therefore we developed a Transmural Trauma Care Model (TTCM). This TTCM consists of four equally important components: 1) intake and follow up consultations by a multidisciplinary team consisting of trauma surgeon and hospital based trauma physical therapist, 2) coordination and individual goal setting for each patient by this team, 3) primary care physical therapy by specialized physical therapists organized in a network and 4) E-health support for transmural communication and treatment according to protocols. The aim of the current study is to assess the cost-effectiveness of the TTCM.

**Methods:**

Patients will be recruited from the outpatient clinic for trauma patients of the VU University Medical Center (VUmc) if they have at least one fracture and were discharged home. A *controlled-before-and-after* study design will be used to compare the TTCM with regular care. Measurements will take place after the first outpatient clinical visit and after 3, 6 and 9 months. Prior to the implementation of the TTCM, 200 patients (50 patients per time point) will be included in the control group. After implementation 100 patients will be included in the intervention group and prospectively followed. Between-group comparisons will be made separately for each time point. In addition, the recovery pattern of patients in the intervention group will be studied using longitudinal data analysis methods. Effectiveness will be evaluated in terms of health-related quality of life (HR-QOL), pain, functional status, patient satisfaction, and perceived recovery. Cost-effectiveness will be assessed from a societal perspective, meaning that all costs related to the TTCM will be taken into account including intervention, health care, absenteeism, presenteeism and unpaid productivity. Additionally, a process evaluation will be performed to explore the extent to which the TTCM was implemented as intended, and to identify possible facilitators and barriers associated with its implementation.

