## Methods

### Design

To answer the research questions, a modified *controlled-before-and-after* study will be conducted at the outpatient clinic for trauma patients of the VU University Medical Center (VUmc), Amsterdam, the Netherlands. The modification of the original study design -in which both control group and intervention group are observed prospectively- is that in our design only the intervention group will be prospectively followed. This modification is required due to the limited resources available. Prior to the implementation of the TTCM, data of 200 control patients who received care as usual will be collected during an inclusion period of 4 months. The control group will consist of 4 clusters of patients who either had their first consultation at the outpatient clinic for trauma patients of the VUmc 0 (i.e. baseline), 3, 6 or 9 months ago. Per cluster, we aim to include approximately 50 patients, all of whom will be asked to fill out an online questionnaire once after providing informed consent. After implementing the TTCM, patients who enter the outpatient clinic for trauma patients of the VUmc and meet the inclusion criteria will be asked to participate in the intervention group of the study. Patients in the intervention group will be prospectively followed for 9 months (*n* = 100) and will be asked to fill out online questionnaires at baseline, 3, 6 and 9 months after their first consultation at the outpatient clinic for trauma patients. See Fig. 1 for a detailed illustration of the study design.

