#### Primary outcome measure

The primary outcome measure is general HR-QOL, measured using the Dutch version of the EQ-5D [20]. The EQ-5D consists of five questions representing five dimensions; mobility, self-care, usual activities, pain/discomfort and anxiety/depression. Each question is scored on a 3 point scale (1–3) with higher scores indicating greater severity level, resulting in a 5 digit index representing one of the 243 health status of the EQ-5D. Using the Dutch tariff, the participants’ EQ-5D health status will be converted into a utility score ranging from 0 (dead) to 1 (healthy). Additionally, quality adjusted life years (QALYs) will be calculated using linear interpolation between measurement points. The EQ-5D shows good psychometric properties in trauma patients with one or more fractures [21–23].

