#### Clinical effectiveness

The clinical effectiveness analyses will consist of two parts. First, the TTCMs’ effectiveness in terms of HR-QOL, pain, perceived recovery, functional status and patient satisfaction compared with usual care will be explored at 3, 6 and 9 months follow-up using regression analyses. The four clusters of control patients (i.e. time after their first consultation at the outpatient clinic for trauma patients respectively 0, 3, 6 and 9 months) will be compared with the patients in the intervention group at the corresponding time points. Second, the recovery pattern of patients in of the intervention group will be studied using longitudinal data analysis in terms of HR-QOL, pain, perceived recovery, functional status and patient satisfaction during the 9 month follow-up period (and while receiving the TTCM). All of the aforementioned analyses will be corrected for confounders if necessary (e.g. age, gender, level of education). Confounding will be checked by adding the potential confounding variable to the crude models, and will subsequently be considered to be present if the regression coefficient changes by 10% or more. All of the clinical effectiveness analyses will be performed in SPSS, using a level of significance of *p* < 0.05.

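### EQ-5D is the single primary outcome but is tested separately at 3, 6 and 9 months, each at 0.05, with no primary time point or contrast

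*Protocol article*

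**What the plan says.** The section Primary outcome measure names one outcome and attaches no time point to it: "The primary outcome measure is general HR-QOL, measured using the Dutch version of the EQ-5D". The Abstract (Methods) says "Between-group comparisons will be made separately for each time point". The section Clinical effectiveness says that the effect "compared with usual care will be explored at 3, 6 and 9 months follow-up using regression analyses", matches each control cluster to the intervention group at the same time, and ends with one rule for everything: "All of the clinical effectiveness analyses will be performed in SPSS, using a level of significance of *p* < 0.05".

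The Design section sets the sample structure. For controls: "Per cluster, we aim to include approximately 50 patients, all of whom will be asked to fill out an online questionnaire once". The 100 intervention patients, by contrast, are the same people at baseline, 3, 6 and 9 months. Longitudinal modelling is kept for that group alone: "In addition, the recovery pattern of patients in the intervention group will be studied using longitudinal data analysis methods".

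The first research question, at the end of the Background, asks whether the care model is effective compared with regular care. For the primary outcome, three tests bear on that question.

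**The concern.** Naming a single primary outcome normally means that the main question gets one answer at the stated significance level. Here it gets three, each at 0.05, and the text does not say which one counts or how they combine. A significant difference at one follow-up time and none at the other two could be reported as effectiveness on the primary outcome. The error rate for that statement is not 5%.

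The design makes this sharper than usual. When both arms of a trial are measured repeatedly, the tests at successive visits are positively correlated through both arms, which tempers the inflation. Here the controls at 3, 6 and 9 months are separate people, so only the intervention arm links the tests.

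**Working it through.** The document gives no power calculation, effect size, standard deviation or overall error rate, so there is no figure of its own to reproduce. The counts agree: 4 × 50 = 200 controls, and 200 + 100 = 300 patients.

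**Inputs from the protocol article**
- About 50 controls per time point, different people, each measured once (Design).
- 100 intervention patients, the same people at each time point (Design).
- Three follow-up comparisons, at 3, 6 and 9 months, each at 0.05 (Clinical effectiveness).

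**Assumptions**
- Tests are two-sided; the text does not state sidedness.
- The standard deviation (SD) is equal across groups and times, and follow-up is complete.
- The within-patient correlation rho in the intervention arm is not given, so a range is shown.

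**Step 1: dependence between the tests.** In SD units, the variance of one time-point difference is 1/50 + 1/100 = 0.03. Two such differences share only the intervention patients, so their covariance is rho/100. Their correlation is (rho/100)/0.03 = rho/3, which cannot exceed 1/3.

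**Step 2: chance of at least one p < 0.05 with no effect at any time.** With independent tests this is 1 − 0.95³ = 14.26%. With correlation rho/3, by numerical integration of the equicorrelated normal distribution:

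| rho | correlation of tests | at least one of three significant |
|---|---|---|
| 0 | 0 | 14.3% |
| 0.3 | 0.10 | 14.2% |
| 0.5 | 0.17 | 14.1% |
| 0.7 | 0.23 | 13.9% |
| 0.9 | 0.30 | 13.6% |
| 1 | 0.33 | 13.5% |

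The unstated rho therefore hardly matters.

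**Step 3: precision of the two candidate primary contrasts.** A single time point, such as 9 months, has SE = √0.03 = 0.173 SD. The equally weighted mean of the three differences has variance (1/50)/3 + (1/100)(1 + 2rho)/3:
- rho = 0.3: 0.00667 + 0.00533 = 0.0120, SE 0.110 SD
- rho = 0.5: 0.00667 + 0.00667 = 0.0133, SE 0.115 SD
- rho = 0.7: 0.00667 + 0.00800 = 0.0147, SE 0.121 SD
- rho = 0.9: 0.00667 + 0.00933 = 0.0160, SE 0.126 SD

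The difference detectable with 80% power at 0.05 is (1.96 + 0.84) × SE: 0.49 SD for one time point and 0.31 to 0.35 SD for the mean. Keeping three separate tests with a Bonferroni level of 0.05/3 would raise the single-time figure to 0.56 SD.

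**Step 4: when the mean helps and when it hurts.** For a constant effect of 0.4 SD, power is 64% for one time-point test and 89% to 96% for the mean (rho 0.9 to 0.3). For an effect of 0.5 SD at one time only, the mean difference is 0.5/3 = 0.17 SD. Its power is then about 28% to 30% (rho 0.7 to 0.5), against 82% for the test at that time.

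**The case against.** The best defence is that the study is exploratory. The Clinical effectiveness section uses the language of exploring effects, the Abstract promises only a first indication of cost-effectiveness, and the Discussion looks ahead to a possible randomized trial. If all three differences are reported and each is read for its own time, each test keeps its own 5% level. A reader might infer that the protocol intends to claim success if any time point is significant. It states no such rule, and the 14% describes what that rule would cost. This part of the objection stands and limits the weight of the point. It does not remove it, because a declared primary outcome with a p < 0.05 threshold leaves that use of the results open.

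It can also be said that an article leaves multiplicity rules to a fuller document. That is fair for a missing rule. But separate comparisons at one common level are a choice this article states, and that choice is what is questioned.

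Two stronger readings are tempting, and the text does not support them:
- **Counting the baseline cluster as a fourth test.** That cluster is also compared with the intervention group, but the effectiveness analysis is set at 3, 6 and 9 months. Baseline is not a follow-up effect test.
- **Saying that separate testing in itself throws precision away.** The smaller SE in Step 3 belongs to a different quantity, a mean over time. With complete data and controls measured once, a group-by-time model gives essentially the same time-specific differences as separate regressions. Using only 50 controls at each time follows from the design. Even unadjusted testing at any of three times has about the same power as the mean (92.5% against 93% at 0.4 SD, rho 0.5), though at the 14% error rate.

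**Conclusion.** The point holds as a modest one. The protocol fixes three separate tests of its single primary outcome at 0.05 and names no primary time point or contrast. With no effect at any time, the chance of at least one nominally significant EQ-5D result is about 14%. This rests on two-sided tests and equal variances, and barely on the within-patient correlation. A conclusion on quality of life drawn from whichever time point is significant would not carry the stated 5% level.

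A gain in precision follows only if the mean over time is chosen as primary and the effect is similar at the three times. Its SE is then 27% to 37% smaller than at a single time point, for an assumed rho of 0.9 to 0.3.

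**What to change.** Name one primary EQ-5D contrast, tested once at 0.05, before the between-group data are analysed. Either option is acceptable:
- **Mean group difference over 3, 6 and 9 months.** Estimate it from one model with group, time as categories and their interaction, allowing for the repeated intervention measures by generalized estimating equations or a mixed model. Fix the equal weights in advance.
- **The 9-month difference alone.** This suits a sponsor who cares most about the end state.

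Report the three time-specific differences with 95% confidence intervals as supportive estimates under both options. If neither is wanted, the alternative is to say plainly that the three comparisons are exploratory estimates, with no confirmatory claim attached to any one of them.

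The cost is a change of wording, with no extra patients, visits or data. The mean dilutes an effect present at only one time, which is why the time-specific results stay in the report. The 9-month option keeps the SE of 0.173 SD and brings no gain in precision. Neither option touches the non-concurrent controls, the selection bias acknowledged in the Discussion, or the data-driven choice of confounders. The 5% level is restored only with respect to multiple time points.

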**Discussion:**

This planned research will give insight into the feasibility of the TTCM model in clinical practice and will give a first indication of the cost-effectiveness of the TTCM and help us to further develop post-clinical trauma care.

**Trial registration:**

Trial registration number: NTR5474. The Netherlands National Trial Register (NTR). Registered 12 October 2015.

## Background

Trauma accounts for 9.6% of global mortality and is the leading cause of death during the first four decades of life [1, 2]. Since trauma patients are typically relatively young, the amount of Disability-Adjusted Life Years (DALYs) lost due to trauma, is larger than from any other disease and causes an important part of worldwide morbidity [3]. Furthermore, major trauma has shown to be the most important cause of long-term functional limitations in adults aged younger than 45 years [4].

The majority of trauma patients have one or more fractures due to their trauma, sometimes in combination with organ system injuries. Fractures of the lower extremities in particular have a major impact on functional status and health-related quality of life (HR-QOL) [5, 6]. Moreover, the economic burden of trauma to society is extensive due to the associated high *direct* as well as *indirect* costs (e.g. absenteeism costs). To illustrate, the total costs per patient with an operatively treated vertebral fracture is estimated to be €66.000, of which the majority (i.e. €47.000) is due to increased absenteeism [7]. Due to the major impact of trauma on mortality, morbidity, and (societal) costs, there has been increased interest in the organization of trauma care over the last three decades. In the literature it is frequently mentioned that trauma care is a chain of services, consisting of pre-hospital care, resuscitation and in-hospital care. During the last two decades, an improved organization of *pre-hospital* and *in-hospital* care by developing specialized trauma centers using Advanced Trauma Life Support (ATLS®) guidelines, has led to a 15–25% decrease in mortality of severe trauma patients [8–11]. Since mortality has decreased significantly due to this re-organization of trauma care, it has been suggested that the focus of trauma care should shift to *improving quality of life and outcome*, rather than on survival of trauma patients, because further improvements in survival rates are likely to be small [8, 11]. To improve quality of life and outcome among trauma patients, more attention for optimizing the rehabilitation phase is crucial. Even though numerous studies investigated the outcome of trauma patients, none of these studies focused on the *organization* and *content* of post-clinical trauma care. It is recognized that serious gaps exist between patients’ transition from acute care to rehabilitation and their return to society [12–14]. Therefore the limited focus on post-clinical trauma care is remarkable. Recently the American Trauma Society developed a post-clinical psychological support program, including self-management and peer support to improve the trauma patients’ psychosocial outcomes [15]. Nonetheless, there is limited attention for optimizing the organization of the post-clinical *physical* rehabilitation of trauma patients in primary care, which may have led to an inefficient and/or suboptimal rehabilitation process. After being discharged from a hospital, the majority of Dutch trauma patients rehabilitates in the primary care setting (i.e. treatment by a primary care physical therapist). In contrast to secondary and tertiary care, however, guidelines and protocols, as well as an interdisciplinary coordination, are lacking in primary care.

Previous research in other patient groups indicates that post-clinical care organized in networks of experienced and specialized healthcare providers is likely to result in better clinical outcomes and lower costs compared to regular care models [16]. Furthermore, a recent feasibility study among osteoarthritis patients showed improvements in health-related quality of life, function, and patient satisfaction when primary care was coordinated by a clinical case manager (mostly a hospital based physical therapist or nurse practitioner) who was in close contact with the surgeon [17]. However, whether such an organization of the post-clinical rehabilitation process of trauma patients also leads to improved treatment outcomes is currently unknown.

The aforementioned considerations led us to develop a new Transmural Trauma Care Model (TTCM) for trauma patients with at least one fracture, aiming to improve patient outcomes by refining the organization and quality of the post-clinical rehabilitation process. The TTCM is a joint initiative of hospital based physical therapists and trauma surgeons working closely together in the development of TTCM. The TTCM consists of four equally important components: 1) intake and follow up consultations by a multidisciplinary team consisting of a trauma surgeon and a highly specialized hospital based trauma physical therapist, 2) coordination and individual goal setting for each patient by this team, 3) primary care physical therapy by specifically trained trauma physical therapists organized in a network and 4) E-health support for transmural communication (between hospital based trauma physical therapist and primary care based physical therapist) and treatment according to protocols. To gain insight to the new care models’ cost-effectiveness a *controlled-before-and-after* study will be conducted [18]. This article describes the study protocol.

The proposed study aims to answer the following research questions:Is the TTCM effective in terms of HR-QOL, pain, functional status, patient satisfaction and perceived recovery compared to regular care in trauma patients with at least one fracture?Is the TTCM cost-effective from a societal perspective (including intervention costs, health care costs, absenteeism, presenteeism and unpaid productivity) compared to regular care?What is the recovery pattern of patients receiving the TTCM in terms of HR-QOL, pain, functional status, patient satisfaction and perceived recovery during the 9 month follow-up period?What are the barriers and facilitators associated with the implementation of the TTCM?What is the reach, dose delivered, dose received, and fidelity of the TTCM?

## Methods

### Design

To answer the research questions, a modified *controlled-before-and-after* study will be conducted at the outpatient clinic for trauma patients of the VU University Medical Center (VUmc), Amsterdam, the Netherlands. The modification of the original study design -in which both control group and intervention group are observed prospectively- is that in our design only the intervention group will be prospectively followed. This modification is required due to the limited resources available. Prior to the implementation of the TTCM, data of 200 control patients who received care as usual will be collected during an inclusion period of 4 months. The control group will consist of 4 clusters of patients who either had their first consultation at the outpatient clinic for trauma patients of the VUmc 0 (i.e. baseline), 3, 6 or 9 months ago. Per cluster, we aim to include approximately 50 patients, all of whom will be asked to fill out an online questionnaire once after providing informed consent. After implementing the TTCM, patients who enter the outpatient clinic for trauma patients of the VUmc and meet the inclusion criteria will be asked to participate in the intervention group of the study. Patients in the intervention group will be prospectively followed for 9 months (*n* = 100) and will be asked to fill out online questionnaires at baseline, 3, 6 and 9 months after their first consultation at the outpatient clinic for trauma patients. See Fig. 1 for a detailed illustration of the study design.

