### Population

A total of 300 trauma patients will be included in the study. Both operatively and non-operatively treated patients will be included, irrespective of whether or not they were admitted to the hospital. In order to be eligible for inclusion, trauma patients have to meet the following inclusion criteria: having at least one traumatic fracture, being aged >18 years, and being able to fill out online questionnaires. In both the intervention- and control group, the duration between the patients’ actual trauma and their first consultation at the outpatient clinic for trauma patients can vary, depending on the treatment that was selected at the emergency department (i.e. admitted to hospital or sent home). Patients will be excluded if they have red flags (i.e. traumatic brain injury, pathological fractures, and/or cognitive limitations), if they do not speak Dutch, if their rehabilitation process takes place in a tertiary care facility, and/or when patients live outside the catchment area of the VUmc.

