### Recruitment

#### Control group

Control group patients will be identified from hospital records. All eligible patients will be contacted by phone by one of the investigators. At this point, patients receive further information about the study, and in- and exclusion criteria will be verified by the coordinating investigator. Patients who are willing to participate and eligible will then receive an email containing a link to an online questionnaire. Clicking the link to the online questionnaire will serve as informed consent. Patients who do not respond within 1 week will receive a reminder email which will be resent after another week of not responding. If the patient does not reply to both emails one of the coordinating investigators will contact the patient by phone to inquire whether the patient is still interested and willing to participate as indicated earlier.

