#### Intervention group

Intervention group patients will be identified during their first consultation at the outpatient clinic for trauma patients. During this consultation, patients will be informed about the study purpose and procedures by one of the investigators. Also, in- and exclusion criteria will be verified. Patients who are willing to participate and are eligible will receive an email containing a link to an online questionnaire. Clicking the link to the online questionnaire will serve as informed consent. Subsequently, patients will be prospectively followed and will receive additional online questionnaires at 3, 6 and 9 months follow-up. Patients who do not respond within 1 week to one of the aforementioned online questionnaires will receive a reminder email which will be resent after another week of non-responding. If the patient does not reply to both emails one of the coordinating investigators will contact the patient by phone to inquire whether the patient is still interested and willing to participate.

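### Groups are compared at nominal months although controls and intervention patients reach the questionnaire by different routes; actual time since first consultation should be recorded and fixed as a covariate

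*Protocol article*

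**What the plan says.** All places are in the Methods of the protocol article.

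- **Design, controls.** The comparator is cross-sectional: "The control group will consist of 4 clusters of patients who either had their first consultation at the outpatient clinic" 0, 3, 6 or 9 months earlier. On size and frequency: "Per cluster, we aim to include approximately 50 patients, all of whom will be asked to fill out an online questionnaire once". On the calendar: "data of 200 control patients who received care as usual will be collected during an inclusion period of 4 months".
- **Design, intervention group.** The same 100 patients "will be asked to fill out online questionnaires at baseline, 3, 6 and 9 months after their first consultation".
- **Recruitment, Control group.** "Control group patients will be identified from hospital records"; an investigator then phones them, checks eligibility and emails the link.
- **Recruitment, Intervention group.** Patients are identified during the first consultation, emailed the link, and later "will receive additional online questionnaires at 3, 6 and 9 months follow-up". The reminder sequence (one week, another week, then a call) is the same as for controls.
- **Data analysis, Clinical effectiveness.** The four control clusters "will be compared with the patients in the intervention group at the corresponding time points". Effectiveness is to be explored at 3, 6 and 9 months. Confounders are corrected for if necessary, with age, gender and education as examples, and count as present if the coefficient changes by 10% or more.

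**The concern.** In the between-group regressions a control's cluster label stands in for elapsed time, and a scheduled mailing does so for an intervention patient. The two are produced differently. An intervention patient has an individual clock that starts at enrolment. A control must first be found in records and reached by phone, and the article does not say whether that call is made as each control reaches the time point or from a list drawn up earlier.

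Patients with fractures can be expected to improve over these months. If so, a group that answers later looks better for that reason alone. Late controls would narrow the apparent benefit of the TTCM on EQ-5D and on the other recovery outcomes. Even without a difference in means, a wider spread of actual times in one group adds noise.

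This is about the interval from first consultation to questionnaire. The interval from trauma to first consultation, which the Population section says can vary in both groups, is a separate matter.

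**Working it through.** **1. Stated figures.** 4 clusters × 50 = 200 controls; 200 + 100 = 300, which agrees with "A total of 300 trauma patients will be included in the study". The article gives no SD, effect size or timing figure, so there is no stated bias or power figure to reproduce.

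**2. What the calendar allows.** The inclusion period is 4 months and the clusters are 3 months apart.

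- If labels were fixed on one list at the start of inclusion, actual times could span 0–4, 3–7, 6–10 and 9–13 months. Neighbouring clusters would overlap by 4 − 3 = 1 month, and with uniform contact the mean lag would be 2 months.
- If each control is called on reaching the time point, the lag is about 0.

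The article does not say which applies. These are the two ends of what its text permits.

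**3. Size for modest lags.** Assumptions, none from the article: EQ-5D SD 0.25; gain of 0.20 over months 0–3 and 0.06 over months 3–6, each linear over 13 weeks; mean lag of controls 2, 4 or 6 weeks.

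- Standard error of a 50 v 100 contrast: 0.25 × √(1/50 + 1/100) = 0.0433.
- Slope, months 3–6: 0.06/13 = 0.0046 per week. Slope, months 0–3: 0.20/13 = 0.0154 per week.
- Shift = slope × lag.

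| Contrast | Lag (weeks) | Shift | Shift / SE |
|---|---|---|---|
| 3 months | 2 | 0.009 | 0.21 |
| 3 months | 4 | 0.018 | 0.43 |
| 3 months | 6 | 0.028 | 0.64 |
| 0 months | 2 | 0.031 | 0.71 |
| 0 months | 4 | 0.062 | 1.42 |
| 0 months | 6 | 0.092 | 2.13 |

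A control who is late for 3 months lies on the 3–6 month segment, so the flatter slope applies there. The steep slope is met only by late controls in the 0-month cluster.

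**4. Sensitivity to the SD.** With SD 0.20 or 0.30 the standard error is 0.035 or 0.052. The 3-month shifts then run from 0.009/0.052 = 0.18 to 0.028/0.035 = 0.80 standard errors.

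**5. Effect on the test.** With no true effect, the two-sided 5% rejection rate is Φ(b/SE − 1.96) + Φ(−b/SE − 1.96), where b is the shift. At SD 0.25 the 3-month rows give 0.055, 0.071 and 0.098. Most of these rejections would go against the TTCM.

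**6. Fixed-list end.** A 2-month mean lag at 3 months gives 2 × 0.06/3 = 0.04, or 0.04/0.0433 = 0.92 standard errors, with a rejection rate of 0.152. This carries the 3–6 month slope on to 7 months, so it is too large if recovery flattens after 6 months.

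**The case against.** The strongest reply is that nothing shows the times to differ. Both groups are anchored on the first consultation with the same nominal months. Rolling contact fits a 4-month inclusion period well, and a cluster labelled 0 months could hardly come from one list worked through over four months. Both groups answer through an emailed link with identical reminders; the only extra steps for controls are the record search and the recruitment call, and nothing says the call comes after the due date. The list of confounders is open, so elapsed time could be entered. Contact windows are commonly left to a full protocol or analysis plan, and the design figure is missing from the available text.

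Most of this stands. A reader might infer that unequal timing has in fact entered the TTCM effect; the article gives no elapsed times and does not support that. A reader might also take the shift of about 2 standard errors as applying to the effect estimates. It needs a 6-week mean lag on the assumed early slope, so it concerns only the 0-month comparison, which is a baseline contrast and not one of the three effectiveness time points. Nor is the absence of a contact window a finding in itself.

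What the reply does not remove is the stated analysis. The comparison is by nominal time point, the two groups are ascertained differently, and elapsed time is considered only if someone nominates it and it passes the 10% rule. A variable expected to predict every recovery outcome should not depend on that.

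**Conclusion.** The point holds as an unprotected risk, not as a demonstrated bias. Actual time since first consultation can differ between groups, most plausibly at 0 months, where a control must be traced and phoned after a visit at which an intervention patient would already have been enrolled. If controls answer later and patients are still improving, the TTCM effect is understated.

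The effect is negligible under prompt rolling contact. Under the stated assumptions it is modest at 3 months for lags of 2 to 6 weeks, and it approaches one standard error only if lists were fixed in advance. No slope is assumed after 6 months, so no figure is offered for the 6- and 9-month contrasts. Confidence in the size is low because the lag, the slopes and the SD are all assumed. The change is still worth making, because it costs little and replaces a label with the quantity it stands for.

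**What to change.** 1. Derive weeks from first consultation to questionnaire completion for every questionnaire in both groups, and report its distribution by group and time point.
2. Include it as a fixed covariate in each between-group regression instead of leaving it to the 10% rule.
3. Use actual rather than nominal time in the intervention group's recovery model.
4. Send each control's link at the same interval since first consultation that triggers the intervention group's questionnaire.

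Cost: one derived variable and one degree of freedom per regression. The consultation date should be in the hospital record; that the online system stores a completion date is an assumption, as the article does not say so. If timing overlaps poorly between groups, the adjusted contrast loses precision and leans on the assumed form of the time trend. Step 4 limits that by aligning the times at source, and the distributions from step 1 would show whether it remains a problem.
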